## Study Report

A complete study report and its results shall be written on completion of the study and will include any conclusions drawn with respect to the safety and efficacy of the study product (refer to ICH Topic E3 - Note for Guidance on Structure and Content of Clinical Study Reports (CPMP/ICH/137/95)).

Starpharma may also request the preparation of an interim report for submission to a regulatory agency. Starpharma or its agent will write the report in consultation with a nominated Investigator (or nominee). It is the expectation of Starpharma that the Investigator will sign the final study report.

Progress reports will be provided to the NIH, FDA, IRB/IEC and all other relevant regulatory bodies in accordance with their requirements.

# INDEMNITY AND COMPENSATION

Starpharma will provide compensation to participants for any injury suffered as a result of participation in the study in accordance with the Medicines Australia Guidelines for compensation for injury resulting from participating in a company-sponsored research project. A copy of the Medicines Australia Guidelines is available to participants from the research staff on request.

In the event that participants suffer an injury as a result of participating in this research project, care and treatment will be provided by the public health service at no extra cost to the participant.

## Insurance

Starpharma has taken out insurance to cover its obligations under Indemnity and compensation guidelines for injury to healthy volunteers involved in the Study.

# SPONSOR RESPONSIBILITIES

In addition to preparing the study protocol, the Sponsor or its agent will also be responsible for the conduct of the activities listed below.

## Funding

All direct costs associated with the conduct of the study and laboratory investigations will be paid for by Starpharma as outlined in the Clinical Trial Agreement. Starpharma will be reimbursed by NIAID for the cost of conducting this study.

## Supply of Study Materials and Study Documentation

Starpharma or its agent will supply the study materials including CRFs, subject Diary Cards and other associated documentation required for the study.

## Compliance with Regulatory Requirements

Starpharma will ensure that the Investigator is conducting the study in accordance with the local and international regulatory requirements as stipulated in the protocol.

## Transfer of Sponsor Obligations

Transfer of Sponsor Obligations may occur for certain activities such as monitoring and data management.

# USE OF DATA AND PUBLICATIONS

The principles for publication of Results of this study will be addressed in Clinical Trial Agreements between Starpharma and NIAID, and Starpharma and the subcontractors performing the study.

[Note: Results means any and all information and know how (whether patentable or not) which is discovered, invented or developed or which arises in the course of or as a result of the conduct of the Study, including any and all improvements to the products being studied.]

## Declaration of Helsinki

The Declaration of Helsinki can be found at the following link:

<http://www.wma.net/e/policy/b3.htm>

## Outcomes, Diagnostics and Follow-Up Evaluations

| **Condition** | **Study gel Use** | **Evaluation** | **Follow up and Treatment Action** |
| --- | --- | --- | --- |
| Deep Epithelial Disruption (Ulceration) | Hold study Gel (until evaluated) | Swab for herpes simplex culture.  Perform syphilis serology (Herpes serology optional) | Re-evaluate in 48-72 hours and reinstate study gel use if resolved. If the ulcer has become worse or not healed in 48-72 hours follow the lesion per local standard of care. Ask participant to return in 7-10 days for follow up syphilis serology. If there is reoccurrence and there is no other aetiology, then consider permanent discontinuation. |
| Superficial Epithelial Disruption (Abrasion/Peeling) | Continue | Naked eye evaluation | Re-evaluate by speculum examination in 48-72 hours. If condition is significantly worse, hold study gel use. Otherwise continue study gel use. |
| Localised erythema or oedema: area of less than 50% of vulvar surface or combined vaginal and cervical surface | Continue | Naked eye evaluation | If asymptomatic, re-evaluate at next regularly scheduled visit. If symptomatic, re-evaluate by speculum examination in 5-7 days. If worsened significantly, hold study gel use, until further evaluation is scheduled. Otherwise, continue study gel use. |
| Generalised erythema or severe oedema; area of more than 50% of vulvar surface or combined vaginal and cervical surface affected by erythema | Hold study Gel (until evaluated) | Naked eye evaluation | Re-evaluate in 48-72 hours and reinstate study gel use if resolved. If there is reoccurrence and there is no other aetiology, then consider permanent discontinuation. |
| Abnormal vaginal discharge (not considered due to gel leakage) | Hold study gel (until evaluated) | Perform wet mount for Candida vaginitis, trichomoniasis, and BV | Provide treatment for all cases of trichomoniasis, symptomatic Candida vaginitis, and symptomatic bacterial vaginosis. Gel use to be paused until 5 days after both cessation of treatment and symptoms for all cases of symptomatic Candida vaginitis, and symptomatic bacterial vaginosis. Gel permanently discontinued and subject withdrawn in cases of trichomoniasis. Gel use may be continued without treatment in the presence of asymptomatic Candida vaginitis and/or asymptomatic bacterial vaginosis |
| Unexpected genital bleeding | Continue (at clinician’s discretion) | Naked eye evaluation | If determined to be due to deep epithelial disruption, refer to guidelines in this table. Otherwise continue gel use. |
| Presumed cervicitis (findings on exam such as mucopurulent cervical discharge) | Hold study gel (until evaluated) | Evaluate for N. gonorrhoeae and C. trachomatis | Provide treatment and permanently discontinue gel use / withdraw participant for all cases of cervicitis. |
| EAE that is judged by the site investigator or designee to be definitely, probably, possibly, or probably not related to the study gel or applicator | For Grades 1,2, and 3 – Hold study Gel (until evaluated)  For Grade 4 – Permanent Discontinuation / withdraw participant | Evaluate as according to current clinical practice at the site  Not applicable | Provide treatment as clinically indicated, when resolved reinstate study gel use at clinician’s discretion.  Not applicable |

1. The 0 hour sample will be taken between 2–10 minutes after dose application. [↑](#footnote-ref-2)
2. Minimum 5 day wash-out between Treatment periods. [↑](#footnote-ref-3)
3. Three separate CV samples will be taken on different days at a minimum 24 hours between samples [↑](#footnote-ref-4)
4. Hepatitis B antigen, anti-HCV antibodies, anti-HIV antibodies with associated information and counselling [↑](#footnote-ref-5)
5. Pap smear performed unless documented result (within 12 months) available [↑](#footnote-ref-6)
6. Including pelvic examination [↑](#footnote-ref-7)
7. If necessary, the study participant may stay overnight at the clinical unit. [↑](#footnote-ref-8)
8. AEs reported pre-first study dose will be recorded as “screening/baseline signs and symptoms” [↑](#footnote-ref-9)

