## Study Procedures

## Pre-dose sampling

Following enrolment the participants will be given three CV sampling kits and asked to provide three separate samples from three separate days. The samples should be taken at least 24 hours apart during the intra menstrual period (i.e. should not include menses). The participants will not be required to attend the study centre and will be able to send the samples into the clinical unit by courier, however if they experience difficulty undertaking the sampling, they may attend the clinical unit and be assisted by female staff. The courier will be in the form of a taxi service, regularly used by the clinical study site for this function, and the sample will be stored in refrigerated conditions on ice packs in an opaque, insulated container during transit. The sample will be marked as an uninfected biological sample; however the nature of the sample will not be identifiable to the courier to protect the privacy of the study subject. The sample is to be transported to the study centre within 24 hours of collection, if not; the sample is to be repeated.

During this period, any AEs reported will be recorded as screening/baseline signs and symptoms, and medications recorded as concomitant medication.

## Treatment Period 1

The first treatment period will include the following procedures:

- Review of the inclusion/exclusion criteria
- Review of screening/baseline signs and symptoms pre-dose and AEs post dose and concomitant medications
- Pregnancy test
- Randomisation to a sampling sequence
- Condom and sexual restrictions counselling (see Section 7.4.4)
- Administration of 3% SPL7013 Gel by study participant. If the study participant is not considered to be able to administer the product correctly after training during screening, or is uncomfortable doing so, a female member of the study team may administer the product.
- CV sampling using the INSTEAD SoftCup at 0, 1, 3, 12 or 24 h post application according to the randomization schedule. A time window of within 5 minutes is permissible for the 0 and 1 hour time points, and within +/-10% of the time for the 3, 12 and 24 hour time points (see Section 7.2.1)

Study participants will be permitted to leave the clinical unit between study treatment administration and CV sampling, except when a time 0 or 1 hour sample is to be collected. If necessary, study participants may stay overnight at the clinic.

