## Toxicity Management

AEs and laboratory abnormalities will be graded as outlined in Section 8 .

For the purpose of monitoring toxicities, the baseline value is defined as the last value prior to the administration of the first dose of study medication. All management is based on changes from this value.

All grade 2 or higher laboratory abnormalities should be confirmed by repeat testing as soon as possible, preferably within 3 calendar days of receipt of results prior to dose interruption or discontinuation, unless such a delay is not consistent with good medical practice.

In response to AEs reported by study participants and/or observed upon exam by study staff, the study site investigator or designee will recommend either continuation or holding study gel use consistent with the criteria in Section 16.3. Study gel use also will be held or discontinued in the event of an expedited adverse event (EAE) that is judged by the site Investigator or designee to have a potential causal relationship with study product.

Unless the participant withdraws consent, she will remain in the study to complete the safety evaluations (unless clinically contraindicated according to Section 16.3).

Study participants who develop an RTI (i.e. bacterial vaginosis (BV) or candidiasis) requiring treatment whilst on study will not be withdrawn, but study product will be suspended until symptoms have resolved and treatment is completed as outlined in Section 7.4.5. However, study participants who develop an STI during the study period are to be withdrawn from the study.

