## Pausing / Stopping Rules

The study will be paused if:

- 2 or more participants report a grade 3 or higher genital AE, considered to be related to study medication or
- Ulceration considered to be related to study medication and with no clear explaination is seen in 2 or more participants or
- study product is discontinued in 3 or more participants due to genital events considered to be related to study medication

In the event that a decision is taken to pause the study according to the above criteria, a full review will take place of all the AE data for all subjects by the Principal Investigator, DAIDS Medical Officer, Medical Monitor and Starpharma. The ethics committee and DAIDS are to be immediately notified of this decision. By reviewing the full data along with the data emerging from the ongoing study(ies) and that from existing studies, the team will come to a decision based on their judgement and expertise as to the next course of action, which could be:

1. To restart the study with no amendment to the protocol
2. To restart the study after implementation of a protocol amendment.
3. To place the study on clinical hold pending the emergence of further data.
4. To terminate the study

The ethics committee, TGA, FDA, and DAIDS are to be notified of any protocol amendment, study hold, or termination of the study according to applicable regulations as outlined in Sections 9.6 and 11.

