## EAE Reporting Requirements for this Study

EAE Reporting Level

This study uses the Intensive Level of EAE reporting as defined in the DAIDS EAE Manual.

Study Agents for Expedited Reporting to DAIDS

The study agents that must be considered in determining relationships of AEs requiring expedited reporting to DAIDS are: 3% SPL7013 Gel, applicator and INSTEAD SoftCup.

Study Agents for Expedited Reporting to Starpharma Pty Ltd

The study agents that must be considered in determining relationships of AEs requiring expedited reporting to Starpharma Pty Ltd are: 3% SPL7013 Gel.

Grading Severity of Events

The severity of adverse events will be graded according to Section 8.3.

EAE Reporting Periods

AEs must be reported on an expedited basis at the Intensive Level during the Protocol-defined EAE Reporting Period, which is:

The entire study duration for an individual participant (from study enrolment until study completion or discontinuation of the participant from study participation for any reason).

After the end of the Protocol-defined EAE Reporting Period stated above, the site must report serious, unexpected, clinical suspected adverse drug reactions if the study site staff becomes aware of the event on a passive basis, i.e., from publicly available information.

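### The SoftCup is a named study agent for EAE causality, but the EAE row of Section 16.3, the EAE hold in Section 8.5 and the three pause criteria do not cover events attributed to it alone

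*Protocol*

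**What the plan says.** **Agents for causality.** Section 8.7.2 (EAE Reporting Requirements for this Study) lists the agents to be considered for expedited reporting to DAIDS as "3% SPL7013 Gel, applicator and INSTEAD SoftCup". For reporting to the sponsor it lists the gel only. The EAE reporting period runs "from study enrolment until study completion or discontinuation of the participant from study participation for any reason".

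**Action for one participant.** The EAE row of Section 16.3 covers an EAE judged "definitely, probably, possibly, or probably not related to the study gel or applicator". Grades 1 to 3 lead to a gel hold until evaluation. The Grade 4 line reads "For Grade 4 – Permanent Discontinuation / withdraw participant". Section 8.5 (Toxicity Management) also calls for gel to be held or discontinued for an EAE "judged by the site Investigator or designee to have a potential causal relationship with study product"; the synopsis gives the study product as the gel.

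**Action for the study.** The Pausing / Stopping Rules have three criteria. The first is "2 or more participants report a grade 3 or higher genital AE, considered to be related to study medication". The second is ulceration in two or more women that is related to study medication and lacks a clear explanation. The third is "study product is discontinued in 3 or more participants due to genital events considered to be related to study medication".

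**SoftCup exposure.** Section 2.4 acknowledges that inserting and removing the cup may cause mild irritation. Section 7.1.2.1 places the home sampling after enrolment: "Following enrolment the participants will be given three CV sampling kits".

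**The concern.** The protocol treats the SoftCup as an agent that can cause a reportable event, but its mandatory responses are not connected to that judgement. The list in the EAE row differs from the DAIDS list by the SoftCup alone. The row already reaches beyond the drug to a device, the applicator, so leaving out the other device looks like an oversight rather than a principle.

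At stake is the safety of healthy women who gain no direct benefit. If an event is put down to the cup, no EAE rule requires that gel or sampling be held, or that a woman with a Grade 4 event be withdrawn. Such events also do not count towards a pause, although each further treatment period brings another insertion.

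**Working it through.** The point rests on comparing texts; the plan has no figure to reproduce. Take an event caused by the SoftCup and judged Not Related to both gel and applicator.

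**1. Mandatory triggers**

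| Rule | Relationship required | Met by this event? |
|---|---|---|
| EAE reporting to DAIDS (8.7.2) | gel, applicator or SoftCup | Yes |
| EAE row, Grades 1–3 hold (16.3) | gel or applicator | No |
| EAE row, Grade 4 withdrawal (16.3) | gel or applicator | No |
| EAE hold (8.5) | study product | No |
| Pause criteria 1, 2 and 3 | study medication | No, 0 of 3 |

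Study medication is not formally defined. Section 10.2.2.1 speaks of its application, which points to the gel. The second pause criterion excludes the event twice, since an ulcer traced to the cup has an explanation.

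**2. What still acts whatever the cause**

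Of the 8 rows in Section 16.3, four open with a gel hold regardless of cause: ulceration, generalised erythema or severe oedema, abnormal discharge, and presumed cervicitis. All cervicitis leads to withdrawal, and so does trichomoniasis under the discharge row. Two limits apply:

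- For recurrent ulceration or generalised erythema, permanent discontinuation is considered only if no other aetiology is found. A cup injury is another aetiology.
- A hold or withdrawal under these rows does not count towards a pause unless the event is related to study medication.

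**3. Which events escape**

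The EAE row includes the category probably not related. By the definitions in Section 8.3 this applies when the agent cannot be excluded. A post-dose EAE therefore escapes the row only if judged Not Related to both gel and applicator.

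**4. Exposure, from the schedule**

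- SoftCup insertions per woman: 1 (screening) + 3 (pre-dose) + 5 (post-dose) + 1 (follow-up) = 10. For 12 women: 12 × 10 = 120.
- Gel doses per woman: 5. For 12 women: 12 × 5 = 60.
- Insertions before any gel: 1 + 3 = 4 per woman. By Section 7.1.2.1 three of these follow enrolment, so they lie inside the EAE reporting period. An EAE from one of them cannot be related to gel or to a gel-filled applicator.

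**The case against.** The best defence is that the two lists serve different purposes. Section 8.7.2 governs reporting and sets the agents by recipient, with the gel alone for the sponsor. Section 16.3 governs gel use, as its action column is headed. A product-hold rule limited to the product could be deliberate. This does not settle the matter, because the EAE row already covers the applicator and because its Grade 4 line withdraws the participant, which is more than a decision about gel.

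The second defence is that much protection remains, and this largely stands:

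- Besides the cause-neutral rows, Section 7.4.5 suspends study visits for treated vaginal infections.
- Section 7.1.2.2 repeats the eligibility review before the first dose, and Section 5.1.3 requires all criteria to be met. A woman harmed during home sampling can be stopped there.
- Section 8.5 has the investigator recommend continuing or holding gel in response to reported or observed AEs.
- Sections 9.2, 9.6 and 12.12 allow withdrawal, termination or suspension, and Section 8.2.2 sends every SAE to the sponsor within 24 hours, whatever its cause.
- A gel hold also stops insertions in later periods, since each treatment-period sample follows a dose.

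A reader might infer that SoftCup harm leads to no action at all. The list above shows otherwise. A reader might also infer that a 12 h or 24 h sample already due must be taken from an injured woman. No text compels that; Table 1 lists vaginal sampling as an endpoint, not a safety procedure, and she or the investigator may stop at any time.

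What does not stand is the idea that discretion makes the trigger unnecessary. The protocol chose mandatory triggers for gel and applicator.

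**Conclusion.** The gap is real but narrow. It covers an EAE, or a genital AE of grade 3 or higher, that is attributed to the SoftCup and judged Not Related to gel and applicator. For individual action the event must also fall outside the cause-neutral rows of Section 16.3. No mandatory EAE hold, Grade 4 withdrawal or pause then applies. What is left is the Period 1 eligibility review and discretion.

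The point is minor. It concerns participant safety only, and no endpoint is biased. It assumes that study medication means the gel. The pre-dose example also rests on Section 7.1.2.1, since Section 7.2.1 has the sampling kits handed out at the screening visit; the post-dose and follow-up insertions do not depend on that timing.

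It would go too far to say that events involving the cup can never pause the study. After dosing the cup enters a gel-exposed vagina, and Section 6.9 lists irritation as a gel risk, so many events would be judged possibly related to gel and would count. The protocol gives no rate of severe SoftCup events, so no probability of a missed pause can be derived from it.

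**What to change.** - **Section 16.3, EAE row:** extend the relationship to *the study gel, applicator or INSTEAD SoftCup*. For EAEs related to the SoftCup, hold both gel and SoftCup sampling at Grades 1–3. At Grade 4, permanently discontinue both and withdraw the participant.
- **Section 8.5:** name the SoftCup beside study product in the sentence on EAE holds.
- **Pausing / Stopping Rules:** in all three criteria, widen the relationship to *study medication, applicator or SoftCup*.

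Do not add an automatic hold on pending samples after every genital finding regardless of cause. That would give up endpoint data for findings unrelated to the cup, and is better left to the investigator.

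The cost is protocol wording and one added causality field on the AE page, with no extra visit or test. A woman whose sampling is held may lose a time point, 1 of her 5 post-dose samples for each dose affected.
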